**Description of the population to be studied (inclusion/exclusion criteria)**

Once a signed consent is obtained, the participant is enrolled in the study and screened for the presence of varicose veins as defined by the chronic venous disorders Clinical-Etiology-Anatomy-Pathophysiology (CEAP) classification system as (1) demonstrating a Varicose Veins score >0 at the prospective site of product application and (2) demonstrating an Active Ulcer Number equal to zero at the prospective site of product application.

*Inclusion Criteria:*

- Participants at least 19 years of age or older.
- Participants with lower limb varicose veins.

*Exclusion Criteria*

- Allergy to witch-hazel or any allergies in the cream.
- Intent to undergo surgical treatment varicose veins within the next six weeks.
- Pregnant or breastfeeding or planning to be pregnant.

- Any Dementia or Major Cognitive dysfunction that would preclude the individual's ability to provide informed consent or complete the Case Report Form.
- Any unstable medical condition (including but not limited to cardiovascular, cardiac/hypertension disease, moderate to severe kidney disease, and moderate to severe liver disease)
- Any medical condition that would preclude the participant's or a caregiver's ability to administer the product on a daily basis for the time period required to complete the study.
- An active ulcer at the site of product application (as evaluated during CEAP screening).

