**Introduction/Context:**

It is estimated that chronic venous disease in the lower extremities (e.g. varicose veins) is one of the most common pathological conditions in adults within industrialized countries, affecting ~40% of the population. Chronic venous disease can encompass numerous pathologies whose casual factors can be both genetic and/or environmental and express a wide scope of symptomatic presentations from ulcers, deep vein thrombosis, and varicose veins. The latter refers to a tortuous or twisted vein(s) that may be visibly enlarged or protrude physically due to the engorgement of blood within the peripheral lower limb vasculature. Mechanically, this deformation and poor blood flow is related to the reduction in tensile strength and function of veins leaflets that typically ensure a unidirectional movement of blood. The loss of leaflet function causes blood reflux, localized pooling, and architectural obstructions which give rise to varicose veins.

Within Canada treatments for varicose veins can be segmented into two regulatory sections, the Therapeutic Products Directorate (TPD) that oversees drug and medical device usage and the Natural and Non-prescription Health Products Directorate (NNHPD) that oversees products deemed to originate from natural sources rather than human-derived innovations. With respect to NNHPD products and varicose veins, plant extracts from witch-hazel (*Hamamelis virginiana*) and horse-chestnut (*Aesculus hippocastanum*) are the primary natural medicinals used to treat this condition. The sponsor (Delivra Inc.) currently holds a Natural Product Number (NPN) license for the manufacturing and sales of topical LivRelief™-Varicose (NPN 80029345) that includes 10% (w/w) witch-hazel. In keeping with the vast majority of NPNs the efficacy of this hinges upon the ingredients-specific Health Canada monograph for topical witch-hazel. This is the inverse to TPD drugs, which undergo rigorous product-specific testing to generate a product-specific monograph.

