Recently, the NNHPD has signaled a broad reconstruction of its claim system to better distinguish those products that have undergone product-specific clinical testing as opposed to those which rely upon ingredient-specific monographs. The underlying goal is to provide the Canadian consumer with sufficient scientifically-underpinned information and labeling to make informed purchases. With this in mind, the sponsor (Delivra Inc.) is interested in completing an study of its current product for its current claim within the scope and limitations as described by the product license. In essence, a Phase-IV interventional pilot study is proposed.

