**Absorption and Plasma Level:**

To our knowledge there is no scientific information (peer-reviewed or otherwise) regarding the topical absorption, distribution, metabolism, or excretion of witch-hazel extract or a component thereof.

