#### *Exploratory analysis:*

- Evaluation of statistical differences (if any) in objective and/or subjective measures at onset and completion of the trial.

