### Schedule of Assessments

As described in Table 2, on Day 1 of the study the participant completes the Informed Consent Form (ICF), is evaluated according to inclusion and exclusion criteria, undergoes CEAP classification of the region in question, photographed within and limited to the region in question, limb diameter measurement, and Q-LES-Q-SF in this chronological order. On the same day and subsequent to these evaluations and measures the product is applied for the first time (Day 1) and materials and instructions are provided for self-administration over the proceeding period (41 days).

At the end of six weeks (42 days +/- 3 days) the same schedule of assessments is administered (with the exception of consent, pregnancy test and inclusion/exclusion) as well as self-reported adverse events, if any.

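### Protocol V4 does not exclude or record current or recent users of the marketed study cream, so some onset values may already be on-treatment values

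*Supplement*

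**What the plan says.** All references are to Protocol V4 (May 2017).

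- **Market status.** Introduction/Context says that the sponsor "currently holds a Natural Product Number (NPN) license for the manufacturing and sales of topical LivRelief", and that the aim is a "study of its current product for its current claim within the scope and limitations as described by the product license".
- **Eligibility.** There are two inclusion criteria: age 19 or over, and "Participants with lower limb varicose veins". The seven exclusions cover allergy, planned surgery ("Intent to undergo surgical treatment varicose veins within the next six weeks"), pregnancy or breastfeeding, cognitive dysfunction, unstable medical conditions, inability to apply the product, and active ulcer. None concerns past or current use of the cream.
- **Recruitment.** Participant Recruitment and Advertising names patients of one clinic who have varicose veins, and people answering posters there. The investigator takes a health history.
- **Timing.** Schedule of Assessments places consent, eligibility, baseline measures and first application on Day 1: "On the same day and subsequent to these evaluations and measures the product is applied for the first time (Day 1". Table 2 has no row for prior use.
- **Use of the onset values.** The exploratory analysis is "Evaluation of statistical differences (if any) in objective and/or subjective measures at onset and completion of the trial". The primary endpoint is completeness of the data, and Statistical Analysis sets two 70% feasibility criteria.
- **Pharmacology.** Absorption and Plasma Level says that "there is no scientific information (peer-reviewed or otherwise) regarding the topical absorption, distribution, metabolism, or excretion of witch-hazel extract".

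Protocol V3 has the same exclusion list, so the latest version does not mend the gap.

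**The concern.** The study recruits people who have the condition the cream is sold for. Someone who applied it on the morning of Visit 1 meets every listed criterion. For that person the Day 1 application is not the first exposure, and the onset measurement falls in the middle of treatment.

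Two results are exposed. The design has no control group, so each participant's onset value is the only comparator. If it is an on-treatment value, the change to week 6 reflects continuing the cream, not starting it. The second is the skin-reaction count. Safety and Adverse Events names rash as a known reaction that calls for stopping the product, so a person still using the cream is more likely than a new user to be someone who has not reacted.

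If prior use is not recorded at Visit 1, neither effect can be identified or reliably corrected afterwards.

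**Working it through.** No figure in the plan is at stake. N=30 is given in Study purpose and rational without a derivation, so there is nothing to reproduce. The check has two parts: reading the text, then scaling the consequence under stated assumptions.

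**1. Can a current user enrol?**
- The cream is licensed for sale, so prior use is possible.
- Neither of the two inclusion criteria and none of the seven exclusions removes a user. The allergy exclusion removes known reactors, not tolerant users.
- Consent, baseline and first application share Day 1, so there is no washout.
- The health history could bring prior use to light, but no rule makes it an exclusion or a recorded variable.

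So yes, a current user can enrol.

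**2. Effect on the mean change.** Let f be the share of current users (assumed; the documents give none) and D the mean change in new users.
- If users have no further change to make, pooled mean = (1 - f) × D. With 3 of 30, f = 0.10 and the mean is 10% lower. With 9 of 30, f = 0.30 and it is 30% lower.
- If users still show a fraction g of D, pooled mean = [1 - f(1 - g)] × D. With g = 0.5 (assumed), the loss halves: 5% at f = 0.10 and 15% at f = 0.30.

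**3. Effect on a paired comparison.** Assumptions: two-sided 5% paired t-test, n = 30, within-group SD of change 1, standardised change d in new users and zero in users. The pooled mean is d(1 - f), the pooled SD is √[1 + f(1 - f)d²], and power comes from the noncentral t distribution with 29 degrees of freedom.

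Example, d = 0.5 and f = 0.30: mean 0.35; SD √(1 + 0.21 × 0.25) = 1.026; effective d = 0.35/1.026 = 0.341; power 44%.

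| Share of users f | Power, d = 0.5 | Power, d = 0.6 |
|---|---|---|
| 0 | 75% | 89% |
| 0.10 | 65% | 80% |
| 0.20 | 55% | 70% |
| 0.30 | 44% | 57% |
| 0.50 | 25% | 33% |

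The same test in never-users alone at f = 0.30 (n = 21) has power 59% for d = 0.5 and 74% for d = 0.6. Under these assumptions, separating the groups gives a better test than pooling, despite the smaller n.

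**4. Effect on skin reactions.** Assume a risk r in new users and near zero in established users. Then P(at least one) = 1 - (1 - r)^m, with m new users.

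| Assumed r | m = 30 | m = 27 | m = 21 |
|---|---|---|---|
| 1% | 26% | 24% | 19% |
| 2% | 46% | 42% | 35% |
| 5% | 79% | 75% | 66% |

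The expected count, r × m, falls by the factor (1 - f) whatever r is. The protocol calls rash rare and gives no rate, so the low rows may be nearer the case.

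**The case against.** **This is a feasibility pilot.** The primary endpoint is data completeness and success is judged on two 70% criteria. Prior use hardly touches these. Established users might complete more readily, but the documents give no direction or size for that. This stands, and it limits the point to the exploratory comparison and the skin-reaction count.

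**The bias is toward zero, and there is no control group.** Diluted change would not create a false benefit, and the change could not be attributed to the cream even in never-users. Both are true. But a comparison that is planned should at least start from an interpretable onset.

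**A Phase IV study may admit existing users.** That is a defensible choice. It argues for recording prior use, not for leaving it unknown.

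**The schedule speaks of a first application on Day 1.** In context this is the first study application. It screens nobody out.

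**Stronger readings the documents do not support.**
- A reader might infer that the cohort is pre-selected for people who tolerate the cream. Recruitment is through the clinic and posters, not among users, and nothing shows that any user will enrol.
- A reader might infer that nobody will ask about earlier use. The Case Report Form is not shown and a health history is taken. One can say only that the protocol specifies no such question and no rule that acts on the answer.
- A reader might take the lack of absorption data as evidence of carry-over. It neither shows nor excludes a lasting local effect. It only means that the documents give no basis for assuming any particular interval is long enough.

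**Conclusion.** The gap is real and limited. As written, the criteria admit current or recent users of a marketed cream, with baseline and first study application on one day, so the sample may include people whose onset values are on-treatment. To the extent that they enrol, the exploratory change is pulled toward zero and the skin-reaction count is biased low.

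The size depends on f, which the documents do not give and which could be zero. The factor (1 - f) also assumes that users have no further change to make; someone moving from irregular to twice-daily use could still change, and the loss would then be smaller. The effect sizes and rash risks above are illustrations. The primary feasibility result is little affected. The point still merits a change, because the information is cheap to collect at Visit 1 and hard to recover later.

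**What to change.** Add a question on current and prior use of the cream (NPN 80029345), including date of last use, to the Visit 1 eligibility check and the Case Report Form. Then choose one of two routes and state it in the protocol:

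1. **Exclude.** Add current or recent use of the study cream to the exclusion criteria, and define what counts as recent. The sponsor must justify the interval, since the documents offer no basis for one. Barring any use ever would be wider than the problem requires.
2. **Keep and separate.** Admit prior users, but name never-users as the main exploratory result for the onset-to-completion change and for skin reactions, with prior users shown separately.

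The cost is one extra question at Visit 1, plus a slightly smaller candidate pool (route 1) or a never-user subset below 30 (route 2).

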#### **Participant Recruitment and Advertising:**

Patients of the Mayer Institute suffering of varicose veins will be offered to participate in the study. Participants will also be recruited through advertisements (posters) at The Mayer Institute in Hamilton. The participant will contact the study investigator (they physician) and make an appointment to discuss the study and obtain consent. Each participant will be initially screened by a trained research coordinator, and then assessed by the principal investigator for health history and meeting of the inclusion criteria and ensure they do not meet any of the exclusion criteria (see below).

#### **Study Design and Methodology:**

The present study is designed as a phase IV interventional pilot study.

#### **Statistical Analysis:**

As described by Thabane et al. (2010), we have assigned success criteria based on the following feasibility objectives:

- At least 70% of all eligible participants can be recruited
- Complete full data collection in at least 70% of all recruited participants

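### Eligibility is assessed only after consent and no offers or refusals are counted, so the 70% recruitment criterion cannot show poor uptake; 'recruited' also needs a definition before it can serve as the completeness denominator

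*Supplement*

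**What the plan says.** All references are to Protocol V4 (May 2017), the latest version in the Supplement.

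- **Statistical Analysis** consists of two success criteria: "At least 70% of all eligible participants can be recruited" and "Complete full data collection in at least 70% of all recruited participants". Neither 'eligible' nor 'recruited' is defined.
- **Description of the population to be studied** fixes the point of enrolment: "Once a signed consent is obtained, the participant is enrolled in the study and screened for the presence of varicose veins". The active-ulcer exclusion is likewise judged at the CEAP screening, after enrolment.
- **Schedule of Assessments** gives the same order for Day 1: "the participant completes the Informed Consent Form (ICF), is evaluated according to inclusion and exclusion criteria, undergoes CEAP classification of the region in question". The rows of Table 2 also start with consent.
- **Participant Recruitment and Advertising** names two sources. For the clinic: "Patients of the Mayer Institute suffering of varicose veins will be offered to participate in the study". Poster readers contact the investigator and "make an appointment to discuss the study and obtain consent". It adds: "Each participant will be initially screened by a trained research coordinator, and then assessed by the principal investigator". It mentions no record of how many people are offered the study, respond to a poster or refuse.
- **Study purpose** proposes N=30 without saying whether these are consented, eligible or treated participants. **Definition of endpoints** makes data collection and completeness of datasets the primary endpoint.

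**The concern.** A recruitment criterion is useful only if low uptake can make it fail. For that, the denominator must contain people who could have joined and did not. Here the only eligibility assessment whose timing is stated takes place in people who have already joined, and those who decline leave no trace in any described record. One of the pilot's two success criteria would then say nothing about uptake, and refusals not noted during recruitment cannot be reliably reconstructed afterwards.

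The second criterion uses 'recruited' as its denominator. If that means everyone enrolled at consent, it includes people who fail screening a few minutes later and can never have an end-visit dataset. Screen failure would then be counted as failure to collect data, which is the primary endpoint.

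**Working it through.** **Inputs from the protocol.** N = 30 (Study purpose); both thresholds 70% (Statistical Analysis); enrolment at consent, before eligibility assessment (population section and Schedule of Assessments). The protocol gives no derivation of N = 30, so there is no figure to reproduce.

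**Inputs assumed.** The documents give neither a screen-failure rate nor an expected completeness. I vary the number of screen failures *s* among 30 enrolled, and take a true completeness of 85% among confirmed-eligible participants, with 80% and 90% alongside.

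**Recruitment criterion, two readings of 'eligible'.**

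1. *Confirmed eligible.* Ratio = (eligible and enrolled) / (eligible). Everyone confirmed eligible was enrolled first, so numerator and denominator are the same people and the ratio is 100% for any uptake. Dividing all enrolled by eligible does not help: with 6 screen failures it gives 30/24 = 125%, which is not a proportion.
2. *Those approached who appear suitable.* Ratio = 30 / (number approached). It can fail: 30/42 = 71.4% passes, 30/43 = 69.8% fails and 30/100 = 30% fails clearly. But nothing in the protocol records the number approached, so it cannot be calculated.

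Under neither reading would the study, run as written, distinguish 30 of 42 from 30 of 100.

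**Completeness criterion, if 'recruited' means enrolled at consent.** Complete sets needed: 0.70 × 30 = 21. With *s* failures, only 30 − *s* people can supply a complete set.

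- Completeness needed among eligible participants = 21 / (30 − *s*).
- Chance of passing = P(X ≥ 21), X ~ Binomial(30 − *s*, *p*).

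| Screen failures *s* (assumed) | Needed among eligible | Pass, *p* = 80% | Pass, *p* = 85% | Pass, *p* = 90% |
|---|---|---|---|---|
| 0 | 21/30 = 70.0% | 0.939 | 0.990 | 1.000 |
| 1 | 21/29 = 72.4% | 0.892 | 0.978 | 0.998 |
| 2 | 21/28 = 75.0% | 0.818 | 0.951 | 0.995 |
| 3 | 21/27 = 77.8% | 0.713 | 0.901 | 0.985 |
| 6 | 21/24 = 87.5% | 0.264 | 0.505 | 0.786 |

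**The same criterion with confirmed-eligible participants as denominator.** The pass mark becomes 70% of (30 − *s*), rounded up: 21/30, 19/27 and 17/24 for *s* = 0, 3 and 6. At *p* = 85% the chance of passing is 0.990, 0.986 and 0.980, so it hardly depends on screen failure.

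**The case against.** - **'Eligible' may mean clinic patients offered the study.** That group exists before consent, and both inclusion criteria (age 19 or over, lower limb varicose veins) could plausibly be known for an existing patient. On this reading the criterion is not automatically met. This stands, so a reader should not conclude outright that the criterion is met by construction. But the protocol describes no count that would supply this denominator, so the criterion becomes incalculable instead.
- **The coordinator's initial screen is not dated relative to consent.** True of the recruitment section. The order rests on the population section and the Schedule of Assessments, and those are explicit. Even if some check came first, no record of it or of refusals is described.
- **The two criteria suggest different meanings of 'recruited'.** The first implies that the recruited are a subset of the eligible, which would keep screen failures out of the second. This stands. A reader might infer that screen failures necessarily enter the completeness denominator; the documents do not support that. They support only that the term is undefined and that one plain reading, enrolled at consent, brings them in.
- **Large completeness effects need many screen failures.** Also true. Six failures of 30 is 20%, which may be high for recruits drawn largely from patients with known varicose veins. One or two failures lower the chance of passing only from 0.99 to 0.98 or 0.95 at 85% completeness.
- **Recruitment is not the primary endpoint, and counting rules are commonly left to an analysis plan.** The first part limits severity. The second applies to definitions, but not to the tally: an analysis plan cannot supply refusals that nobody recorded.

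**Conclusion.** The concern holds in two parts of unequal firmness.

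The recruitment criterion, as written, is either met automatically or cannot be calculated. In neither case can it reveal poor uptake. This follows from the protocol's own order of events and the absence of any described count of offers or refusals, and needs no assumed rate.

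The completeness criterion has an undefined denominator. The damage is conditional: it arises only if 'recruited' means enrolled at consent, it is small with one or two screen failures, and it becomes serious only with several (0.90 with 3 and about 0.50 with 6, at an assumed 85% completeness). It would be too strong to say that this criterion is broken or that neither criterion can inform anything.

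The point is worth correcting before recruitment starts, but does not threaten the study as a whole, because the primary endpoint is completeness of data rather than recruitment.

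**What to change.** Amend Statistical Analysis to define three separate proportions, and add the record that the first one needs.

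1. **Recruitment** = those who consent / those on a pre-consent tally. The existing research coordinator keeps the tally without identifiers. It lists clinic patients offered the study and poster responders who appear to meet the two inclusion criteria on information already available before consent, and it notes refusals. No test or extra questioning before consent is needed. Poster readers who never make contact remain uncounted, and the report should say so.
2. **Screen failure** = those found ineligible after consent / those who consent, reported separately so that it affects neither of the other two figures.
3. **Completeness** = participants with all Visit 1 and Visit 2 assessments / confirmed-eligible participants who received the first application on Day 1.

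State also which of these groups N=30 refers to.

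The cost is a few lines of protocol text and a short log kept by existing staff; visits, assessments and treatment do not change. The recruitment percentage will probably look less favourable, because it will now be able to fall below 70%.
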